## Abstract

**Objective:**

Alzheimer’s disease (AD) is characterized by complex pathological mechanisms involving neuroinflammation, oxidative stress, and vascular dysfunction. Remote Ischemic Conditioning (RIC) has shown potential in addressing these pathways by improving cerebral blood flow, reducing oxidative stress, and modulating inflammatory responses. This protocol focuses on evaluating the safety, feasibility, and preliminary efficacy of RIC as a multi-target intervention for delaying cognitive decline in patients with mild Alzheimer’s dementia, aiming to improve cognitive outcomes and overall quality of life.

**Methods and expected results:**

This study is a randomized, controlled, single-center, prospective clinical trial designed to evaluate the safety, feasibility, and preliminary efficacy of RIC in patients with mild Alzheimer’s dementia. Eligible participants will be recruited and randomly assigned to either the RIC group or a control group receiving sham RIC, with 20 patients in each group. Participants will receive either RIC or sham RIC once daily over a 3-month period. Outcome measures will assess cognitive function, psychological well-being, and inflammatory and neurodegenerative biomarkers. Psychiatric adverse events will be monitored throughout the treatment using the Hamilton Anxiety Rating Scale (HAMA) and the Hamilton Depression Rating Scale (HAMD-17). Cognitive function and daily living abilities will be evaluated at baseline, 3 months, 6 months, and 12 months post-treatment using the Mini-Mental State Examination (MMSE), Montreal Cognitive Assessment (MoCA), Clinical Dementia Rating (CDR), and the Activities of Daily Living (ADL) scales. In addition, blood samples will be collected at each time point to measure plasma biomarkers of *β*-amyloid species and serum inflammatory cytokines to assess potential changes in cognitive decline, disease progression, and inflammation. The primary endpoint is safety, with the expectation that RIC will not increase psychiatric adverse events as reflected in HAMA and HAMD-17 scores. Primary efficacy endpoints include improvements in MMSE, MoCA, CDR, and ADL scores, indicating potential cognitive benefits and enhanced daily functioning. Secondary endpoints will analyze biomarkers to evaluate disease progression and inflammation levels before and after treatment.

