### Outcomes for efficacy

The secondary outcomes of this study are categorized into three classes. Cognitive function and daily living abilities will be evaluated using the MMSE, MoCA, and CDR scales, while daily living abilities will be assessed using the ADL scale. Disease severity and progression will be measured through plasma biomarkers, including Aβ40, Aβ42, the Aβ42/Aβ40 ratio, pTau217, pTau181, GFAP, and NfL. Neuroinflammation levels will be assessed via serum levels of IL-1β, IL-6, IL-8, IL-10, IL-2R, TNF-*α*, ESR, and CRP. These outcomes aim to comprehensively evaluate the efficacy of RIC in addressing cognitive decline, daily living abilities, disease biomarkers, and neuroinflammation in patients with AD.

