### Statistical analysis

Data will be obtained from all patients who complete the study protocols and follow-ups and will be analyzed using the per-protocol (PP) approach. Statistical analysis will be performed using SPSS version 20 (SPSS Inc., Chicago, IL, United States), with a significance level of *p* < 0.05. Demographics and clinical characteristics will be analyzed using descriptive statistics. Continuous and categorical data will be reported as mean values, standard deviations, number values, and percentages. Continuous variables following a normal distribution will be compared using the independent samples *t*-test, ANOVA, or rank-sum test, while categorical variables will be compared using the chi-square test.

In our RIC trial in mild Alzheimer’s dementia (*n* = 40), we implemented two strategies appropriate for small-sample longitudinal data. First, single random forest imputation was applied to address missing cognitive scores (e.g., MoCA/MMSE) by using predictors such as baseline Aβ42/Aβ40 ratio and RIC adherence preserve variable interaction structure. Second, Generalized Estimating Equations (GEE) will be used to model outcome trajectories under the assumption of missing at random (MAR), thereby accommodating incomplete data without imputation. Attrition is minimal (7% MoCA loss at 12 months) and APOE subgroup analyses show no evidence of differential dropout. This approach balances methodological rigor with feasibility and aligns with CONSORT recommendations for early-phase trials with limited resources.

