The assessment of cognitive function and daily living abilities using scales such as the MMSE, MoCA, and CDR reflects the study’s primary clinical outcomes of interest (36). These tools are widely recognized for their sensitivity and specificity in detecting changes in cognitive performance and functional status in mild Alzheimer’s dementia (8, 37), making them reliable measures for evaluating therapeutic impact of RIC. Similarly, biomarkers like Aβ40 and Aβ42, p-tau181, p-tau217, and NfL will be used to monitor disease progression and neurodegeneration (38–41). These markers are central to the pathological cascade in AD, providing insights into the molecular mechanisms modulated by RIC. Longitudinal measurement of these biomarkers enables a detailed analysis of RIC’s capacity to influence amyloid metabolism, tau pathology, and neuronal integrity (5, 42).

In addition, inflammatory cytokines, including IL-6, TNF-*α*, and CRP, will be measured to assess RIC’s effect on neuroinflammation (20, 22, 43–46). Given that neuroinflammation is a key driver of AD pathology, modulating these pathways represents a plausible mechanism through which RIC may exert its neuroprotective effects (36, 38). The inclusion of these markers facilitates a more comprehensive understanding of both systemic and central inflammatory responses to RIC.

The reliability of these parameters in supporting the study’s hypothesis is reinforced by their established roles in AD research and their responsiveness to therapeutic interventions. Neuropsychological scales are routinely employed in clinical trials to detect clinically meaningful changes in cognition and function (36). Likewise, biomarkers like Aβ and tau are well-characterized indicators of AD pathology, with fluctuations in their levels correlating with disease progression (22, 36, 38, 47, 48). Inflammatory cytokines, extensively studied as markers of immune system activity, provide insight into the inflammatory environment associated with AD (22, 48).

Furthermore, the multi-timepoint design of the study—evaluating outcomes at baseline, 3 months, 6 months, and 12 months—enhances the robustness of the findings. This approach allows for the assessment of both immediate and sustained effects of RIC, ensuring that observed changes result from the intervention rather than transient or external factors.

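### The protocol article ranks MMSE, MoCA, CDR and ADL as primary efficacy endpoints in the abstract and as secondary outcomes in the outcomes section, with no lead scale or visit and one p < 0.05 threshold

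*Protocol article*

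**What the plan says.** The protocol article ranks its efficacy measures in three places.

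- **Abstract, Methods and expected results.** Safety comes first: "The primary endpoint is safety, with the expectation that RIC will not increase psychiatric adverse events". The four scales follow: "Primary efficacy endpoints include improvements in MMSE, MoCA, CDR, and ADL scores". Biomarkers come last: "Secondary endpoints will analyze biomarkers to evaluate disease progression and inflammation levels before and after treatment".
- **Outcomes for efficacy.** The section opens: "The secondary outcomes of this study are categorized into three classes". The first class contains the same four measures: "evaluated using the MMSE, MoCA, and CDR scales, while daily living abilities will be assessed using the ADL scale". The other two classes are the plasma biomarkers and the inflammatory markers.
- **Discussion.** Assessing cognition and daily living, with MMSE, MoCA and CDR given as examples, "reflects the study’s primary clinical outcomes of interest". ADL is not named there.

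Statistical analysis sets one threshold, "with a significance level of" p < 0.05. It lists a t-test, ANOVA or rank-sum test for group comparisons, and also plans generalized estimating equations (GEE) for outcome trajectories. The scales are measured at baseline and at 3, 6 and 12 months. No section singles out a scale or a visit for the efficacy conclusion.

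**The concern.** One measure cannot be both a primary and a secondary endpoint of the same trial. The rank decides how a result may be described. As the text stands, a p-value below 0.05 on one of the four scales could be reported as a positive primary efficacy result by citing the abstract. If all four were null, they could be called secondary by citing the outcomes section. Both descriptions would be faithful to the published protocol.

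The sample size section gives 20 per group by precedent, with no effect size or power, and the trial is meant to inform a Phase II study. A chance result carrying a primary label would weigh more in that planning than it deserves.

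**Working it through.** **1. The ranks side by side**

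| Place | Safety | MMSE, MoCA, CDR, ADL | Biomarkers |
|---|---|---|---|
| Abstract | primary | primary efficacy | secondary |
| Outcomes for efficacy (safety: Outcomes for safety) | primary | secondary | secondary |
| Discussion | not ranked | called primary in loose wording, ADL not named | not ranked |

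Safety and the biomarkers keep the same rank wherever one is given. Only the four scales change.

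**2. Inputs for the size of the problem**

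- Scales affected: 4 (abstract; Outcomes for efficacy).
- Post-baseline visits: 3, at 3, 6 and 12 months (Neuropsychological assessments).
- Threshold: 0.05 (Statistical analysis). Sidedness is not stated; two-sided is assumed.
- Correlation between tests: not given. Values of 0.5 and 0.7 are assumptions.

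The article states no number of comparisons and no familywise error rate, so there is no figure of its own to reproduce.

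**3. Chance of at least one false positive, independent tests**

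Formula: 1 − (1 − 0.05)^k for either direction; 1 − (1 − 0.025)^k for results favouring RIC only.

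- Each scale tested once, k = 4: 1 − 0.95^4 = 0.185. Favourable only: 1 − 0.975^4 = 0.096.
- Each scale tested at each visit, k = 4 × 3 = 12: 1 − 0.95^12 = 0.460. Favourable only: 1 − 0.975^12 = 0.262.

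**4. Allowing for correlation**

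For k normal test statistics with common correlation ρ and z = 1.96, the chance is

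1 − ∫ φ(u) [Φ((z − √ρ·u)/√(1 − ρ)) − Φ((−z − √ρ·u)/√(1 − ρ))]^k du.

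| k | ρ = 0 | ρ = 0.5 | ρ = 0.7 |
|---|---|---|---|
| 4 | 18.5% | 15.6% | 13.0% |
| 12 | 46.0% | 31.9% | 23.2% |

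A simulation of t-tests with 20 per arm was run for the 12 tests, with correlation between outcomes of 0 to 0.5 and between visits of 0 to 0.8. It gave about 29% to 46%.

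**5. The count over all outcomes, for comparison**

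Outcomes for efficacy lists 4 scales, 7 plasma markers and 8 inflammatory markers: 19 outcomes × 3 visits = 57. Independent tests give 1 − 0.95^57 = 94.6%, with 57 × 0.05 = 2.85 false positives expected. Of these 57, 15 × 3 = 45 are biomarker comparisons, whose rank is not in dispute.

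**The case against.** Several points on the other side carry weight.

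- **Safety is consistently the primary endpoint.** The abstract, the safety outcomes and the sample size section agree on this, and efficacy is described as preliminary. The abstract's phrase could be read as a lead tier within efficacy, below safety. That softens the conflict but does not remove it: the outcomes section has no such tier and puts the scales level with the biomarkers.
- **The Discussion wording is rationale, not an endpoint designation.** This is right. The contradiction rests on the abstract and the outcomes section alone.
- **A multiplicity rule, lead scale and lead visit may sit in an analysis plan that is not shown.** Their absence is therefore not an error in itself. But an analysis plan cannot apply a rule to the primary efficacy endpoints until it is settled which they are, and this article gives two answers.
- **Testing at every visit is not stated.** GEE on trajectories could give one test per outcome. That is why the four-test figure stands beside the twelve-test one.

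A reader might infer that 57 comparisons make an efficacy signal near certain by chance. The documents do not support that. The 94.6% needs independent tests and counts results in either direction. At a common correlation of 0.5 it falls to 65%. Counting only results in favour of RIC, simulation gives 35% to 76% over the correlations tried. The article also does not say that each outcome is tested at each visit, and 45 of the 57 comparisons are secondary in both places.

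Nor is it established that pTau231, which is measured but absent from the outcome list, has been dropped as an outcome, because that list is not worded as exhaustive.

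**Conclusion.** The contradiction stands. The same four scales carry two ranks in one document, and because both ranks are stated, neither condensation into a journal article nor an unseen analysis plan explains it.

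Its consequence is a substantial inflation of the chance of a false claim on a scale labelled primary: 18.5% with one independent test per scale, and 46% with independent tests at all three visits, against a nominal 5%. At assumed correlations of 0.5 to 0.7 the twelve-test figure falls to about 32% to 23%. All these figures count either direction, assume two-sided testing and no true effect, and take the abstract's ranking as the operative one. The primary role of safety is not in question.

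**What to change.** Use one hierarchy throughout the article: safety as the only primary endpoint, and all cognitive, functional and biomarker outcomes secondary or exploratory. Correct the abstract and the Discussion to match Outcomes for efficacy.

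Name in advance one lead efficacy scale at one visit; MoCA change at 3 months, the end of treatment, would be one example. With a single lead test, its false-positive rate is 5%. Report the other efficacy outcomes as estimates with 95% confidence intervals and make no confirmatory significance claims for them. A formal adjustment such as Holm within each class is an alternative, but a matter of preference.

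The cost is wording only, with no change to visits, measurements or sample size. The downside is that fewer results can be called significant.

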**Conclusion:**

This trial aims to determine the safety, feasibility, and potential effectiveness of RIC as a multi-target intervention for mild Alzheimer’s dementia by integrating cognitive and neuropsychological assessments with biological markers, providing a foundation for future studies.

## Introduction

With the global population aging, Alzheimer’s disease (AD) has become one of the most prevalent neurodegenerative disorders, posing a substantial challenge to healthcare systems. The prevalence of AD is approximately 5% among individuals aged 65 and older, rising to 33.3% in those aged 85 and above (1). As this demographic shift continues, the development of effective prevention and treatment strategies for AD grows increasingly urgent (2, 3).

The hallmark pathological features of AD include the deposition of *β*-amyloid (Aβ) plaques and tau protein tangles in the brain (4). Its progression involves multiple interconnected mechanisms, including neuroinflammation, oxidative stress, and vascular abnormalities, which contribute to the disease’s complexity (5–7). Most approved treatments for AD focus on symptom management rather than altering disease progression (8, 9). Newer approaches, such as anti-amyloid monoclonal antibodies, have shown potential in modifying disease progression but are limited by side effects and challenges in crossing the blood–brain barrier (2, 8–11). Given the multifaceted nature of AD, multi-target interventions that address multiple pathways may be more effective in slowing disease progression (12).

Early diagnosis and intervention are essential, especially in mild Alzheimer’s dementia, where symptoms remain subtle but represent a critical window for therapeutic intervention (13). Treating AD in its mild stage may help prevent the disease’s transition to more severe stages, ultimately preserving cognitive function and reducing the burden on healthcare resources (4, 11, 14–16).

Remote ischemic conditioning (RIC) is a non-pharmacological, non-invasive intervention that has shown promise in activating neuroprotective signaling pathways (15, 17, 18). By enhancing cerebral blood flow, reducing oxidative stress, and modulating inflammation, RIC has demonstrated potential in preventing cognitive decline and improving cognitive function in conditions like vascular cognitive impairment (VCI) (15, 16, 19, 20). Given its multi-target mechanism, RIC could also offer neuroprotective benefits in AD by addressing similar pathophysiological processes (12, 20–22).

This early-phase trial is designed to assess the safety, feasibility, and preliminary efficacy of RIC in slowing cognitive decline in patients with mild Alzheimer’s dementia. By evaluating the tolerability and safety of daily RIC over 3 months and its effects on plasma biomarkers and inflammatory factors, this study aims to lay the groundwork for future research on RIC as a potential intervention for AD-related cognitive decline.

## Subjects and methods

### Study design

This study was registered on www.chictr.org.cn in November 2024 (ID: ChiCTR2400092245) and approved by the Ethics Committee of Beijing Luhe Hospital, Capital Medical University, China (2024-LHKY-092-03). All study participants were fully informed about the research process, risks, and benefits, and voluntarily agreed to participate by signing an informed consent form. The study protocol and informed consent form were approved by the Ethics Committee.

A total of 40 participants will be randomly assigned to either the observation group (RIC group) or the control group (sham RIC group), with 20 participants in each group. All participants with AD included in the study will continue receiving standard pharmacotherapy in accordance with established clinical practice guidelines. Each group will begin RIC or sham treatment, administered once daily for 45 min per session over a period of 3 months.

Specifically, our study has established a Data and Safety Monitoring Board (DSMB) composed of independent experts to ensure rigorous oversight of participant safety, data integrity, and scientific validity throughout the trial. The DSMB is responsible for regularly reviewing accumulated safety data, monitoring adverse events, and making recommendations regarding study continuation or modification as needed to protect participant welfare.

### Patient population

Participants will be recruited from the Neurology Outpatient Clinic and Inpatient Department of Beijing Luhe Hospital, Capital Medical University. Inclusion criteria include: (1) a diagnosis of mild Alzheimer’s dementia based on the 2024 core clinical criteria for “Stage 4 Dementia with mild functional impairment” by the National Institute on Aging and Alzheimer’s Association (NIA-AA) (8); (2) objective evidence of cognitive impairment; and (3) cranial CT or MRI scans supporting AD diagnosis.

Exclusion criteria include: (1) the presence of other conditions that could explain memory impairment such as severe anxiety and depression; (2) contraindications to ischemic conditioning, including severe soft tissue injury, fractures, or bilateral peripheral vascular disease of the upper limbs; (3) hemodynamic instability, defined as systolic blood pressure >180 mmHg, diastolic blood pressure >110 mmHg, heart rate <40 bpm or >100 bpm, peripheral oxygen saturation ≤92%, or body temperature ≥38.5°C; (4) life expectancy ≤1 year; (5) poor tolerance to treatment due to circulatory, respiratory, digestive, hematological diseases, or malignancies; (6) coagulation disorders or active bleeding; (7) concurrent inflammatory conditions or use of medications affecting inflammatory cytokine levels; (8) cerebrovascular diseases, including cerebral infarction, cerebral hemorrhage, vascular dementia and small vessel disease, as well as other neurological or systemic conditions such as thyroid dysfunction, epilepsy, Parkinson’s disease, malnutrition, chronic diarrhea, carbon monoxide poisoning, traumatic brain injury, alcohol intoxication, or other serious physical illnesses; and (9) participation in another ongoing clinical trial.

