### Interventions

All study participants will undergo bilateral limb RIC using the Doctormate IPC-906, manufactured by Beijing Renqiao Neuroscience Institute. Electronic tourniquet cuffs will be placed on both arms of each participant (Figure 1).

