**Figure 1 fig1:**
[figure not shown]
Device for remote ischemic conditioning.

Lacking clinical RIC studies in AD populations, there are no intervention data available for direct reference. In a study published in Lancet Neurology, [name] and colleagues demonstrated that a 45 min daily RIC protocol significantly reduced the recurrence of strokes and the incidence of cardiovascular events in individuals with intracranial atherosclerotic stenosis (23). Additionally, AD research on Transcranial Magnetic Stimulation and Transcranial Direct Current Stimulation has shown cognitive improvements with 2 to 6 months of non-pharmacological treatment (24, 25). As an initial to evaluate safety, the duration of RIC in this study has been set at 3 months. In the RIC group, each session will involve five cycles of cuff inflation to 200 mmHg for 5 min, followed by a 5 min deflation period, conducted daily for 45 min. The sham RIC group will follow an identical schedule, with cuff inflation limited to 60 mmHg for 5 min, followed by a 5 min deflation period, repeated five times per session, once daily, for 45 min. The inflation pressure of 60 mmHg was specifically chosen for the sham group based on previous experience and published protocols, as this level of cuff inflation generates sufficient pressure to mimic the sensation of treatment without inducing true limb ischemia or producing significant physiological changes. Participants undergoing sham procedures typically report a credible sensation similar to active treatment, supporting its validity as a placebo. Additionally, this pressure level aligns with previously validated sham protocols used in multiple high-quality clinical trials (e.g., NCT03868007; ChiCTR2000041042), which have demonstrated strong blinding effectiveness and placebo credibility (26, 27).

The RIC intervention requires participants to attend their assigned community health service stations daily during designated time slots for RIC training. At these facilities, they will use specialized RIC equipment to conduct the sessions as outlined in the study protocol. A dedicated team of specialists will be available to provide comprehensive guidance and support throughout the process, ensuring participant safety, promoting treatment adherence, and maintaining the efficacy of the sessions.

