## Outcomes

### Outcomes for safety

The primary safety outcomes of this study are to evaluate the safety profile of RIC. Specifically, the following adverse events will be monitored:

1)  Psychological and Emotional Impact: Clinical observations and previous research have highlighted that patients with AD often experience feelings of helplessness and depression as their cognitive function declines and their ability to perform daily activities diminishes. These emotional challenges can lead to anxiety and fears about disease progression. Additionally, the pressure sensation caused by RIC training may exacerbate these feelings. To address this, the psychological condition of patients will be assessed using the HAMA and the HAMD-17, and the incidence of related adverse events will be calculated.2)  Procedure Tolerability: Instances of participants being unable to tolerate either the RIC or sham RIC procedures, resulting in suspension from the study, will be recorded as adverse events.3)  Physical Injuries: Signs of tissue or neurovascular injury potentially caused by RIC or sham RIC procedures will be monitored. This includes assessments such as palpation of the distal radial artery for pulsation, visual inspection for local edema, erythema, or skin damage, and palpation for tenderness in the affected areas.4)  Vital Sign Monitoring: Participants’ vital signs, including body temperature, respiratory rate, blood pressure, and heart rate, will be recorded to identify any potential systemic effects of the intervention.

All adverse events will be reviewed and independently determined by trained members of the research team who are blinded to the randomization group. These outcomes aim to comprehensively evaluate the safety of RIC and ensure that any risks associated with the intervention are carefully monitored and managed.

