In this study, participant safety is closely monitored through structured safety management protocols. If a participant experiences psychiatric worsening, indicated by significant increases in anxiety or depression scores (HAMA or HAMD-17), an immediate referral to a psychiatrist will be initiated, and psychiatric interventions or modifications to study procedures may be recommended as appropriate. In cases of physical injury, such as tissue damage, neurovascular compromise, or significant pain related to the cuff procedure, the intervention will be immediately paused. A multidisciplinary specialist team, including experts in neurology, cardiology, neurosurgery, and vascular surgery, will promptly evaluate the participant. Treatment will be provided as needed, and the participants will be closely monitored until full resolution. Detailed records of these events will be documented and reviewed by our Data and Safety Monitoring Board (DSMB) to ensure thorough oversight and appropriate follow-up actions.

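### The named upper-limb vascular exclusion applies only to disease in both arms, although every participant is cuffed on both arms

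*Protocol article*

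**What the plan says.** In the protocol article, Patient population, exclusion (2) bars people with contraindications to ischemic conditioning and gives three examples: serious soft-tissue injury, fractures, and "bilateral peripheral vascular disease of the upper limbs". The examples follow the word *including*, so the list is open. Exclusion (5) adds "poor tolerance to treatment due to circulatory, respiratory, digestive, hematological diseases, or malignancies", and exclusion (8) ends with a catch-all for serious physical illness.

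Under Interventions, "All study participants will undergo bilateral limb RIC", and "Electronic tourniquet cuffs will be placed on both arms of each participant". Each RIC session has "five cycles of cuff inflation to 200 mmHg for 5 min". The sham group follows the same schedule with "cuff inflation limited to 60 mmHg for 5 min". Both are given daily for 3 months. The article describes no one-arm version and no move of the cuff to another limb.

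Under Outcomes for safety, limb checks include "palpation of the distal radial artery for pulsation" and inspection and palpation for swelling, skin damage and tenderness. If a physical injury or significant cuff-related pain occurs, "the intervention will be immediately paused" and a specialist team evaluates the participant.

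**The concern.** Limiting the vascular example to disease on both sides would make sense if one arm were treated and the healthy arm could be chosen. Here both arms are always used, so there is no spare arm. As printed, the named example is narrower than the procedure it is meant to guard.

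Two things are at stake. The first is the participant: an arm with impaired circulation could be occluded repeatedly, every day, in someone with dementia. The second is the primary safety outcome, which counts tissue and neurovascular injury. An avoidable injury in an arm that was already diseased would be recorded as a safety event in a group of only 20, and would blur the evidence meant to support a move to Phase II.

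**Working it through.** This is mainly a comparison of texts. The only arithmetic is the exposure of an affected arm.

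**1. Eligibility against procedure.**

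| Element | What is fixed | Section |
|---|---|---|
| Named vascular exclusion | Disease in both upper limbs | Patient population, exclusion (2) |
| Limbs cuffed | Both arms, every participant, both groups | Interventions |
| One-arm or alternative-limb option | None described | Interventions |

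Taking these together, disease in one arm does not meet the named example, and that arm is cuffed if the person is enrolled.

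**2. Do other exclusions catch it by name?**
- Exclusion (2), general term: it can, if the investigator regards one-arm disease as a contraindication. The other two examples carry no condition of side. Only the vascular one does, which invites the inference that one-sided disease was considered and accepted.
- Exclusion (3): no. It covers blood pressure, heart rate, oxygen saturation and temperature, not limb perfusion.
- Exclusion (5): only where circulatory disease causes poor tolerance of treatment. Disease without evident intolerance at screening does not clearly qualify.
- Exclusion (8), catch-all: a matter of judgement.

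**3. Do the limb checks prevent it?** They are listed as safety outcomes for injury potentially caused by the procedure, and the pause follows an injury or significant pain. As described, both act after exposure has begun.

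**4. Exposure of the affected arm in the RIC group.** Inputs from Interventions are 5 inflations of 5 minutes, once daily, for 3 months (taken here as about 90 days). The stated session length is reproduced with four deflations between five inflations: 5 × 5 + 4 × 5 = 45 minutes, of which 5 × 5 = 25 minutes are inflated.

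| Treated for | Inflations | Inflated time |
|---|---|---|
| 1 day | 5 × 1 = 5 | 25 min |
| 7 days | 5 × 7 = 35 | 175 min |
| 30 days | 5 × 30 = 150 | 750 min = 12.5 h |
| 90 days | 5 × 90 = 450 | 2,250 min = 37.5 h |

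The 7-day and 30-day rows illustrate an earlier stop; the article does not name those points. The last row is a ceiling that assumes full adherence and no pause.

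**5. Chance of that exposure and weight of one event.** Allocation to RIC: 20/40 = 50%. One event in a group of 20: 1/20 = 5%. In the sham group the article describes 60 mmHg as too low to cause true limb ischemia, so the concern there is small.

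**The case against.** The strongest reply is that the operative rule is the general term in exclusion (2), and the three conditions are only examples. Since both arms are cuffed, one-arm disease that makes cuffing unsafe is a contraindication to this intervention and is already barred. Not being named is not the same as being eligible. The other two examples apply to one-sided problems, and the vascular wording may simply be loose. This stands in part: an investigator may exclude such a person. But the same comparison cuts the other way, because the vascular example is the only one that carries a condition of side. A rule that has to be read against its own wording to be safe should be reworded.

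A second reply is that the article is condensed, and the full protocol may contain limb screening before treatment. That is fair, and no weight is placed on the absence of a screening procedure. The word limiting the example to both sides, however, is printed in the article.

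A third reply is that the exposure figures are the ordinary dose for anyone in the RIC group and do not measure risk in a diseased arm. This is correct. They show what the arm would be subjected to, not how often it would be harmed. If very few candidates have one-arm disease, the practical effect is correspondingly small.

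Finally, specialist staff support the sessions, the limb checks and the pause are in place, and a DSMB reviews safety data. A full course of 450 inflations in a visibly deteriorating arm is therefore unlikely. These safeguards limit the harm but do not correct the criterion.

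**Conclusion.** The concern holds, in a narrow form. The printed exclusion does not fit the printed procedure: a person with vascular disease in one arm is not excluded by name, could be enrolled, and would have that arm cuffed. In the RIC group this means 5 inflations to 200 mmHg in the first session and at most about 450 over the course.

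The conclusion rests on reading the limiting word in its usual sense of both sides, and on there being no one-arm option, since none is described. No expected number of injuries is claimed. The sample size and the analysis are unaffected. This is a safety-wording correction that is worth making because it bears on the primary outcome and costs almost nothing.

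**What to change.** In exclusion (2), replace the vascular example with *peripheral vascular disease of either upper limb*. This is a one-phrase protocol amendment. The only downside is a possible, very small loss of eligible patients.
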